#### Estimate Outcomes

The outcome is 30-day mortality. We will use the latest, deidentified, and publicly available Nationwide Emergency Department Sample (NEDS) database [110], including visit information from approximately 20% of US EDs. Consider the case with Auto-ML. The likelihood, *L*, that an ED can successfully use machine learning for this scenario is equal to *p*_1_× *p*_2_. *p*_1_ is the probability that a health care researcher in the ED can build a high-quality machine learning model for this scenario using Auto-ML. *p*_2_ is the probability that the ED can successfully deploy the model if it can be built. Using Aim 1(d)’s test results on whether health care researchers can use Auto-ML to achieve model accuracy of at least 95% of the gold standard, we will conservatively estimate *p*_1_’s minimum and maximum values (eg, by fitting a normal distribution and using its 2.5 and 97.5 percentile points). Based on his extensive experience with deploying models [2], [name] ([name]) will conservatively estimate *p*_2_’s minimum and maximum values. For each of *p*_1_ and *p*_2_, we will adopt five levels going from the minimum to the maximum value for sensitivity analysis. The middle level is the default one and is used for hypothesis testing.

For each ED in the NEDS database, we will retrieve the annual number of patients with community-acquired pneumonia. We will simulate whether or not the ED can successfully use machine learning for this scenario based on the likelihood, *L*. If success/not success, for each ED patient with community-acquired pneumonia, we will simulate whether the patient will die or not based on the 30-day mortality rate reported in the paper [2] when using/not using machine learning. The overall outcome estimate combines the expected outcomes for all patients and EDs. The patients’ discharge weights in the NEDS database will be used to obtain national estimates from sample data in the database. We will handle the case without Auto-ML similarly by simulating not using machine learning.

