#### Outcome Evaluation and Sample Size Justification

Outcomes achieved with and without Auto-ML will be compared. We will test the primary hypothesis that using Auto-ML will be linked to reduced mortality. In the most conservative case assuming a proportion of discordant pairs of 10%, a sample size of 1152 patients provides 90% power to notice an OR of 0.53 [2] using a two-sided McNemar test at a significance level of .05. Each year, community-acquired pneumonia incurs 1.5 million ED patient visits [111], giving adequate power to test the hypothesis. To acquire the whole range of possible outcomes, we will do sensitivity analysis by changing the levels of the probabilities *p*_1_ and *p*_2_, 30-day mortality rate, and rate reduction gained by machine learning.

The scenario of end-stage renal disease patients on dialysis will be handled similarly, with the following main differences. The outcome is number of hospitalization days. The health care unit is dialysis facility. For each US dialysis facility, we will obtain its latest annual total number of hospitalization days and patient count from DialysisData.org [112] to fit a Poisson distribution. For each dialysis patient in the facility, we will simulate his/her annual number of hospitalization days using the distribution, as is often done in the literature [113]. We will test the secondary hypothesis that using Auto-ML will be linked to reduced hospitalization days. If the results from a single simulation run appear too skewed, we will conduct multiple runs and then average their results.

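### Aim 3 averages over simulation runs only if the first run looks too skewed, so Monte Carlo noise is left in some impact estimates and removed from others

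*Protocol article*

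**What the plan says.** The simulation is described in the protocol article, Methods, Aim 3.

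- **Adoption.** Under Estimate Outcomes, L is the product of p1 (a researcher can build a good model) and p2 (the ED can deploy it). For each ED, "We will simulate whether or not the ED can successfully use machine learning for this scenario based on the likelihood" L. Each patient's death is then drawn at the published mortality rate with or without machine learning.
- **Levels.** p1 and p2 each take five levels. The middle level is the default and the one used for hypothesis testing.
- **Data.** The ED database is described as "including visit information from approximately 20% of US EDs". Outcome Evaluation and Sample Size Justification adds: "Each year, community-acquired pneumonia incurs 1.5 million ED patient visits".
- **Test.** For mortality, "a sample size of 1152 patients provides 90% power to notice an OR of 0.53", "using a two-sided McNemar test at a significance level of .05". No test or significance level is named for the dialysis outcome, annual hospitalization days.
- **Number of runs.** The last sentence of the dialysis paragraph reads: "If the results from a single simulation run appear too skewed, we will conduct multiple runs and then average their results".

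**The concern.** The number of runs depends on how the first result looks. The article does not say what counts as too skewed, who judges it, or how many runs follow. This is more than detail left to a fuller document: the article states a decision rule, and the rule depends on the result.

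Aim 3 is meant to deliver a national impact estimate and its range over the levels of p1 and p2. Two things are at stake.

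1. Some of the 5 x 5 = 25 combinations of p1 and p2 could rest on one run and others on an average. Differences between them would then mix simulation noise with real sensitivity to p1 and p2.
2. If the runs judged skewed tend to be the disappointing ones, the reported benefit drifts upward. A reader could not tell whether that had happened.

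**Working it through.** **The plan's own figure.** With 10% discordant pairs and an odds ratio of 0.53, the discordant probabilities are 0.10 x 0.53/1.53 = 0.0346 and 0.10/1.53 = 0.0654. An exact two-sided McNemar test at .05 with 1152 pairs has power 0.9000. The stated sample size reproduces and is not in question.

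**Inputs for the noise of one ED run.** From the article: risk ratio about 0.53, 1.5 million visits a year, about 20% of EDs sampled. Assumed, because the article does not give them: N = 0.20 x 1,500,000 = 300,000 sampled visits; K = 500 or 950 EDs; lognormal ED sizes with log-SD 1; baseline mortality m of 3%-8%; L of 0.1, 0.3 or 0.5.

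**Step 1: noise from adoption.** The expected risk reduction is L x m x 0.47. All patients in an ED share one adoption draw, so the relative variance from adoption is (1-L)/L x (sum of squared ED sizes)/N². For lognormal sizes with log-SD 1, the last factor is about e/K = 2.718/K. The relative SD from adoption alone is then:

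| K | L = 0.5 | L = 0.3 | L = 0.1 |
|---|---|---|---|
| 950 | 5.3% | 8.2% | 16.0% |
| 500 | 7.4% | 11.3% | 22.1% |

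The 300,000 visits do not remove this part, because the sampling unit for adoption is the ED.

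**Step 2: noise from the death draws.** If deaths with and without Auto-ML are drawn independently, the added variance of the risk difference is [m(1-m) + (1-L)m(1-m) + L x 0.53m(1 - 0.53m)]/N. At K = 500, m = 3%, L = 0.1 this is 30.9% of the effect, and the total is sqrt(22.1² + 30.9²) = 38.0%. If each patient's draw is shared between the two arms, this part nearly vanishes. The article does not say which design is used.

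**Step 3: totals.** Direct simulation gives a single-run SD of about 6%-14% of the effect at L of 0.3-0.5, and 16%-38% at L = 0.1. The formulas agree to within about a percentage point. For dialysis, with assumed facility numbers, simulation gives about 2%-6%.

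**Step 4: effect on the sensitivity analysis.** The expected effect is proportional to L, so a 10% relative change in L moves it by 10%. With a single-run SD of 10%, the difference between two single-run cells has SD 10% x sqrt(2) = 14%. The noise exceeds the signal in that illustration.

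**Step 5: bias if the trigger is one-sided.** Suppose a run at or above expectation is kept, and one below it is replaced by the average of R runs including itself. For a roughly normal run result the bias is (1 - 1/R)/sqrt(2 x pi) single-run SDs: 0.20 for R = 2, 0.36 for R = 10, 0.39 for R = 100. Applying 0.36:

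- L of 0.3-0.5: 0.36 x 6% = 2.2% to 0.36 x 14% = 5.0% (simulated: about 2%-6%).
- L = 0.1: 0.36 x 16% = 5.8% to 0.36 x 38% = 13.7% (simulated: about 6%-13%).
- Dialysis: 0.36 x 2% = 0.7% to 0.36 x 6% = 2.2%.

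If only clearly unfavourable runs (more than 1.96 SD below expectation) are repeated, the bias is 0.03-0.06 SD. If extreme runs in either direction are repeated, it is about zero.

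**The case against.** **Inflation of the .05 tests.** A reader might infer that re-running after a look raises the false-positive rate. Under a hypothetical null, repeating every non-significant run and pooling does give a two-sided error of .082 to .097. The article does not support this as a finding. Deaths are drawn from rates that already contain the benefit, and dialysis uses a published 15% reduction, so the null is false whenever L exceeds 0. Even under that null, repeating extreme runs in either direction lowers the error (.017 with 2 runs, .003 with 100). In the simulated ED model at L of 0.3 and 0.5, no single run failed to be significant.

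**Upward bias as the expected result.** Skewed need not mean disappointing, and nothing says the team would repeat only unfavourable runs. This stands: the wording permits the bias but does not state it.

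**Scope.** The sentence closes the dialysis paragraph, and the larger figures here are for the ED scenario. The article handles the two scenarios similarly, so reading the sentence across both is plausible but not certain. Estimate Outcomes also says the overall estimate combines expected outcomes, which could suggest that noise is averaged out. Yet outcomes are drawn patient by patient, and the closing sentence shows that one run's result may stand.

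**Low L is a corner.** Aim 1 (d) hypothesises that at least 60% of researchers succeed. At p1 = 0.6, L = 0.1 needs p2 of 0.1/0.6 = 0.17. The article gives no p2, so the case cannot be excluded, least of all at the lower sensitivity levels, but it should not be read as typical.

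**Conclusion.** The concern holds in a limited form. The article sets a result-dependent rule for the number of runs, without a criterion or a count, where a fixed number would serve better at almost no cost.

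The firm consequence is uneven Monte Carlo noise across the reported estimates. In the ED scenario it is appreciable (SD about 6%-14% of the effect at L of 0.3-0.5, 16%-38% at L = 0.1). In the dialysis scenario, which the sentence certainly covers, it is smaller (about 2%-6%).

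An overstated benefit is conditional on a one-sided trigger: about 2%-6% in the ED scenario at L of 0.3-0.5 and 6%-13% at L = 0.1, and none to speak of with a symmetric one. These figures rest on assumed facility numbers and sizes, mortality and L, and on whether draws are shared between arms. The 1152-patient calculation is unaffected. This is a cheap improvement, not a flaw that invalidates Aim 3.

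**What to change.** Replace the conditional sentence with a rule of this kind: for both scenarios and every sensitivity level, a number of independent runs fixed in advance (for example 1000) is always carried out; the mean over runs is the impact estimate, reported with its 2.5-97.5 percentile range over runs.

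With 1000 runs, a single-run SD of 6%-38% gives a Monte Carlo error of the mean of 6%/sqrt(1000) = 0.2% to 38%/sqrt(1000) = 1.2%. The planned hypothesis tests need not be dropped for this.

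The cost is one sentence and more computing time on the existing cluster. No new data, staff or participants are needed.

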### Ethics Approval

We have already acquired institutional review board approvals from UWM and IH for our study.

## Results

Our paper [35] describes our draft method for automating machine learning model selection. The paper shows that compared to the modern Auto-WEKA automatic selection method [25], on six medical and 21 nonmedical benchmark datasets, our draft method reduced search time by 28-fold, classification error rate by 11%, and standard deviation of error rate due to randomization by 36%, on average. On each of these datasets, our draft method can finish the search process in 12 hours or less on a single computer. The results obtained on the medical datasets are similar to those obtained on the nonmedical datasets. The health care researchers in the Veterans Affairs Salt Lake City Health Care System have used our draft method successfully for a clinical research project [114]. One purpose of this study is to improve the draft method so that it can handle larger datasets more efficiently and effectively.

At present, we are writing Auto-ML’s design document. We intend to finish this study by around the year 2022.

## Discussion

Auto-ML will generalize to various clinical prediction/classification problems, as its design relies on no special property of a specific dataset, patient population, or disease. Auto-ML will be tested on nine modeling problems and datasets, each from a distinct health care system. By providing support for common data models (eg, OMOP [88]) and their linked standardized terminologies adopted by a large number of systems, Auto-ML can be used to construct models if attributes required to solve a problem are accessible in a structured dataset or in one of those common data models. This enables data integration and facilitates building models with data from multiple systems. To help users decide whether any data quality issues need to be handled before modeling, Auto-ML will show the numbers of attribute values outside reasonable ranges and numbers of missing values of nonrepeatedly recorded attributes.

The gaps in scope and accuracy mentioned in the introduction exist in many clinical applications. The principles of our approaches to using incomplete medical data and vast attributes generalize to many other clinical applications beyond the two on care management listed in the introduction.

In summary, our new software is designed to efficiently automate machine learning model selection and temporal aggregation of clinical attributes. By making machine learning feasible with limited budgets and data scientist resources, our new software will help realize value from clinical big data and improve patient outcomes. The models that will be built for the two new modeling problems will help improve care management outcomes.

## Abbreviations

AUC: area under the receiver operating characteristic curve
Auto-ML: Automated Machine Learning
ED: emergency department
EDW: enterprise data warehouse
FEV1: forced expiratory volume in 1 second
HIPAA: Health Insurance Portability and Accountability Act
i2b2: Informatics for Integrating Biology and the Bedside
ICD-9: International Classification of Diseases, Ninth Revision
ICD-10: International Classification of Diseases, Tenth Revision
IH: Intermountain Healthcare
NEDS: Nationwide Emergency Department Sample
OMOP: Observational Medical Outcomes Partnership
OR: odds ratio
PCORnet: National Patient-Centered Clinical Research Network
SQL: Structured Query Language
SUS: System Usability Scale
UWM: University of Washington Medicine
Weka: Waikato Environment for Knowledge Analysis
